## Study setting

The Kantonsspital Olten is a university-affiliated community teaching hospital with 245 beds serving ca. 100’000 inhabitants of the eastern part of the Canton of Solothurn, in north western Switzerland. The Department of Internal Medicine comprises an internal medicine unit with 62 beds (ca. 3’300 admissions per year), an acute geriatric unit (45 beds), a palliative care unit (6 beds) and the emergency department. The majority of patients are admitted to the internal medicine unit from the emergency department; the remainder are admitted directly from the community or transferred from other wards or other hospitals.

### *Intervention*

The intervention consists of a checklist (see appendix) given to each physician of the Department of Internal Medicine prior to study start. The checklist will be presented and explained in August 2013 during a “grand round” to all physicians of the department, who will also receive the checklist as a pocket leaflet. The checklist will also be posted on the mobile desk workstations used during ward rounds, and on the intranet. Once a week, a senior physician will reiterate the steps of the prescribing process and the use of the checklist with the medical team on each ward.

### *4.1 Checklist*

The checklist (see appendix) is based on a study by Scott et al. (Scott IA, 2012), who described a 10-step framework to optimize the medication prescription among older people. We used in addition for the configuration of the checklist another eight-step framework proposed under the acronym ACADEMIA (Assess, Comprehensive Geriatric Assessment, Adherence, Development, Emergence, Minimization, Interdisciplinarity, Alertness) (Dovjak P, 2012). We created a simple checklist which should help the physician during busy clinical routine to systematically consider all relevant points for appropriate prescribing, with particular focus on reducing polypharmacy.

Following points are included in the checklist, according to the stepwise process of prescribing (Scott IA, 2012):

1. *Assess current drug use*

The prescriber is encouraged to perform medication reconciliation using the “brown paper bag” method, i.e. asking the patient to bring in all current drugs (Bayoumi I, 2009). This is probably the best way to establish a reliable medication list.

1. *Identify patients at high risk for adverse drug reactions*

The checklist contains a risk score adapted from Carey et al. (Carey EC, 2008). This score indicate the risk of adverse drug reactions according to the presence of 6 patient’s characteristics.

1. *Estimate life expectancy*

The benefits of certain treatments (e.g. treatment with statins for primary prophylaxis of atherosclerosis) may not be realized during the patient’s remaining life span. The estimation of life expectancy is therefore important and has to be taken into account before prescribing a drug. To estimate life expectancy of an individual patient at the bedside is difficult and many factors should be considered. In order to support (but not to replace) this assessment, the checklist contains a risk score adapted from Carey et al. (Carey EC, 2008).

1. *Identification of potentially inappropriate medication*

As a tool for the identification of potentially inappropriate medication, the checklist reports the Medication Appropriateness Index (MAI) (Hanlon JT, 1992). The MAI consists of 10 questions checking indication, dosage, use and costs of a drug.

1. *Monitoring*

The physician is reminded that after changes of therapy or discontinuation of drugs monitoring and re-evaluation are mandatory to rapidly identify possible rebounds of diseases or symptoms, or new medication errors.

*4.2 Use of the checklist*

The medical team on the wards will integrate the use of the described checklist in usual care of all patients hospitalised in the Department of Internal Medicine. The checklist is a tool to improve the application of strategies which are considered standard of care to optimize drug prescriptions and avoid errors or adverse drug events (Scott IA, 2012; Dovjak P, 2012; Meyer-Nikolic VA, 2012).

1. ***Follow-up***

As safety parameter we will assess the all-cause re-hospitalisation rate at 30 days after discharge using administrative data of the hospital. We believe that the re-admission rate calculated only on the basis of re-hospitalisations at the Kantonsspital Olten is representative because the Kantonsspital Olten is the only hospital in the eastern part of the Canton Solothurn and the great majority of patients discharged from the internal medicine unit of the Kantonsspital Olten come back at the same hospital if any new or recurrent problem occur after discharge.

1. ***Data collection***

At the Department of Internal Medicine, Kantonsspital Olten, most patient information (including diagnoses, therapy at admission and discharge, laboratory results, progress notes, etc.) is currently recorded in the electronic patient record. However, some other information, such as one part of the nursing documentation, is still on paper. Data will be collected from the electronic patient records and completed, if necessary, by review of the paper patient records. The medication at admission and discharge of each patient will be reviewed independently by two of the investigators ([name], [name]), who will assess whether the medication is appropriate or inappropriate according to STOPP and START criteria. Discrepancies in this assessment will be resolved by consensus. Following data will be recorded on a standardised case report form: age; gender; place of residence (home or nursing home); number of diagnoses; Charlson Comorbidity Index (Charlson ME, 1987); length of stay; number of medications at admission and discharge; prescription of NSAID, PPI, systemic corticosteroids, metamizol-natrium, potent opiates, at admission and discharge, and whether these prescriptions are appropriate or not; number of potentially inappropriate medicines (PIM) used and number of potentially inappropriate prescribing omissions (PPO), both at admission and discharge; all-cause re-hospitalisation at 30 days.

Only the investigators will have access to the case report forms, which will be stored in a locked cabinet in the office of the investigators at the Kantonsspital Olten. For statistical analysis data will be anonymised.

1. ***Outcomes***

The primary outcome is the reduction of the proportion of patients using inappropriate drugs (PIM) at discharge and the reduction of the number of prescribed medications at discharge.

Secondary outcomes are:

1. the proportion of patients with potentially inappropriate prescribing omissions (PPOs) at admission and discharge,
2. the prevalence of prescription and the rate of inappropriate prescription of following drugs: non-steroidal anti-inflammatory drugs (NSAID); proton pump inhibitors (PPI); systemic corticosteroids; metamizol-natrium (Novalgin™); potent opiates at admission and discharge,
3. the all-cause rehospitalisation rate at 30 days after discharge

in the intervention and in the control group.

1. ***Sample size***

The sample size is determined by the estimated change in the proportion of users of inappropriate drugs at discharge and the expected size of the intervention effect. Given the high prevalence of polypharmacy in elderly patients (58% in Europe according to Gallagher et al., Gallagher P, 2011) and that 34-77% of these patients use at least one inappropriate drug (PIM), we believe that even a reduction of 10% in patients taking inappropriate medications or a reduction of 10% in the prevalence of polypharmacy will be of clinical relevance. To detect an effect of 10% of the checklist (decrease in prevalence of inappropriate drug prescription and/or polypharmacy from 30% at admission to 20% at discharge) with a probability (power) of 90% at a significance level of 0.05, a sample size of 824 patients (412 in each group) will be needed (table 1.). Therefore, we aim to include 900 patients (450 patients in the intervention group enrolled during the period September-November 2013, and 450 patients in the control group who had been hospitalised in September-November 2012).

1. ***Statistical methods***

Basic demographic characteristics, cumulative co-morbidity (Charlson Co-morbidity Index), the type and number of drugs prescribed and the prevalence of inappropriate prescribing at admission and discharge will be compared using the chi-squared test or Fisher’s exact test for categorical variables, and the Mann-Whitney U test for continuous variables. The results will be analysed with an intention-to-intervention analysis, where all subjects are compared in the intervention group regardless of whether the checklist has been used by the physician in charge. All analyses will be performed using STATA software version 11 for Windows (Stata Corp, College Station, Texas, USA).

1. ***Ethical considerations***

The protocol of the study will be submitted to the local research ethics committee (Kantonale Ethikkommission Aargau / Solothurn). Because the aim of the study is only to evaluate an instrument (the checklist) to improve quality of patient care through better implementation of recognised standards of care (such as medication reconciliation and appropriate prescribing), and data are collected as part of the continuous quality assurance programme of the Kantonsspital Olten, no informed consent from patients will be required.

**Table 1.** Sample size required for each group to detect a 10-20% reduction of the prevalence of inappropriate prescription through a simple checklist according to different power and significance levels.

| Prevalence of polypharmacy or inappropriate drug prescription at admission | Prevalence of polypharmacy or inapproriate drug prescription at discharge | Significance level | Power | Sample size for each group | Total sample size |
| --- | --- | --- | --- | --- | --- |
| 30% | 10% | 0.05 | 90% | 92 | 184 |
| 30% | 20% | 0.05 | 90% | 412 | 824 |
| 20% | 10% | 0.05 | 90% | 286 | 572 |
| 30% | 10% | 0.01 | 90% | 127 | 254 |
| 30% | 20% | 0.01 | 90% | 576 | 1152 |
| 20% | 10% | 0.01 | 90% | 397 | 794 |
| 20% | 10% | 0.01 | 80% | 317 | 634 |

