Many interventions aiming at reliably reducing the number of inappropriate medications in elderly patients and at improving the patient’s safety have been studied. Such interventions include for example medication review by multidisciplinary teams or complex multifaceted pharmaceutical care intervention (medication review, consultation, team participation) (Gokula M, 2012; Patterson SM, 2012; Steinman MA, 2010; Topinková E, 2012). Most of these strategies are efficacious for reducing polypharmacy, but are very complex and time-consuming and therefore not easily applicable in the busy clinical daily routine (Gokula M, 2012; Spinewine A, 2007). User-friendly screening tools which can assess the appropriateness of prescribing and do not need a multidisciplinary team do exist. One of the most frequently used is the Beers’ Criteria list, consisting of a list of drugs to avoid in elderly people (Fick DM, 2003). However, most of these tools based on explicit criteria, including the Beers’ Criteria, were developed in the USA or Canada and are hardly applicable in Europe because of the differences in populations, national drug formularies and prescribing attitudes. For example, almost half of the drugs listed in Beers’ criteria are unavailable in European countries (Fialová D, 2005; Gallagher P, 2011). Moreover, explicit (criterion-based) indicators of appropriateness of prescribing are usually drug-oriented or disease-oriented and do not address for example the burden of comorbid disease in the individual patient (Spinewine A, 2007). A research group in Ireland validated a new set of explicit criteria for potentially inappropriate medication use in older adults called STOPP (Screening Tool of Older Person’s Prescriptions) and START (Screening Tool to Alert doctors to Right Treatment) (Gallagher P, 2008). These authors showed also that potentially inappropriate medicines (PIMs) identified according to STOPP criteria and prescribed to patients 65 years or older are significantly associated with avoidable adverse drug events (Hamilton H, 2011). With other tools (implicit approaches) clinicians use information from the patient and published work (instead e.g. of a fixed list of to-avoid-drugs) to make judgements about appropriateness. They address multiple elements of medication prescribing, which are relevant for many different drugs, clinical conditions and settings (Hanlon JT, 1992). These implicit (judgement-based) approaches are flexible, focus on the patient, rather than on drugs or diseases, and are potentially the most sensitive, but they are time-consuming and depend on the user’s knowledge and experience (Hanlon JT, 1992; Spinewine A, 2007).

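### Appropriateness is rated from charts kept by the physicians who get the checklist in 2013 only, and the case report form keeps PIM/PPO counts without the criterion behind each, so a shift in charting could not be traced

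*Protocol*

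**What the plan says.** **Intervention.** The Protocol (Intervention) has the checklist "given to each physician of the Department of Internal Medicine prior to study start", with its steps repeated weekly on each ward. Section 4.1 includes the Medication Appropriateness Index: "The MAI consists of 10 questions checking indication, dosage, use and costs of a drug". The control patients were treated in autumn 2012, before the checklist.

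**Source of the ratings.** Under Data collection, "most patient information (including diagnoses, therapy at admission and discharge, laboratory results, progress notes, etc.) is currently recorded in the electronic patient record", and "Data will be collected from the electronic patient records and completed, if necessary, by review of the paper patient records". On rating: "The medication at admission and discharge of each patient will be reviewed independently by two of the investigators", "who will assess whether the medication is appropriate or inappropriate according to STOPP and START criteria". Discrepancies go to consensus.

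**What is kept.** The case report form lists "number of potentially inappropriate medicines (PIM) used and number of potentially inappropriate prescribing omissions (PPO), both at admission and discharge". It also records, for five drug classes, whether each prescription is appropriate. It does not list the criterion behind a PIM or PPO.

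**What the criteria look at.** The Introduction remarks that "explicit (criterion-based) indicators of appropriateness of prescribing are usually drug-oriented or disease-oriented".

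**Outcomes.** The proportion of patients with a PIM at discharge and the number of drugs at discharge are both named as primary. PPOs and inappropriate use of the five classes are secondary.

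**The concern.** In a before-after comparison the measuring instrument should be the same in both periods. Here part of the instrument is the chart, and the people who write it are the people who receive the intervention. A criterion that turns on a diagnosis or an indication can only be applied to what the record contains. A physician prompted to consider the indication of every drug may also write more of it down. The same prescription could then be rated differently in 2012 and 2013.

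Two independent raters with consensus deal with disagreement between raters. They do not deal with records that differ between years, and masking the raters to year would not either, because the content of the record would itself differ.

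At stake are the first-named primary outcome, the PPO outcome and the five class-level appropriateness ratings. The number of drugs at discharge is not exposed, because counting drugs needs no recorded indication.

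**Working it through.** **1. The chain of reasoning, link by link**

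| Link | Status in the Protocol |
|---|---|
| Checklist prompts a check of indication, in 2013 only | Stated (Intervention; 4.1; Study population) |
| Ratings are made from the routine patient record | Stated (Data collection) |
| Some ratings depend on recorded diagnoses or indications | Supported in general terms by the Introduction; the STOPP/START items are not listed, so the share is unknown |
| Physicians are told to write the indication down | Not stated; 4.1 asks them to consider it |
| Charting is fuller in 2013 | Inference, plausible but not stated |
| Form records which criterion was met | No, only counts |

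**2. Direction.** Fuller charting can act both ways:
- Fewer PIMs, where a drug was rated inappropriate for want of a recorded indication.
- More PIMs, where a newly recorded diagnosis exposes a drug-disease conflict, or where the brown-bag reconciliation in 4.1 lengthens the recorded drug list.
- More PPOs, where a newly recorded diagnosis calls for a drug that is absent.

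**3. The plan's own figure.** Sample size for 30% against 20%, two-sided α = 0.05, power 90%:

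n = [1.960·√(2·0.25·0.75) + 1.2816·√(0.30·0.70 + 0.20·0.80)]² / 0.10² = 391.9, so 392 without continuity correction.

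With the correction: (391.9/4)·[1 + √(1 + 4/(391.9·0.10))]² = 411.7, so **412 per group**, as stated. With the planned 450 per group, power by the uncorrected formula is 93.5%. No number in the plan is disputed.

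**4. How much net re-rating would matter (what-if).** Let p be the true PIM prevalence at discharge in both years (no true effect), and f the net share of PIM patients rated PIM-free in 2013 only because of the chart. f is an assumption; the documents give no value. Then q = p(1 − f), d = p − q, and with n = 450 per group and p̄ = (p + q)/2:

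se₀ = √(2p̄(1 − p̄)/n), se₁ = √((p(1 − p) + q(1 − q))/n)

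P(p-value < 0.05) = Φ((d − 1.96·se₀)/se₁) + Φ((−d − 1.96·se₀)/se₁)

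For p = 0.30 and f = 0.10: q = 0.27, d = 0.03, se₀ = 0.03009, se₁ = 0.03008; 0.168 + 0.002 = 0.169.

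| True prevalence | f | Apparent drop (points) | Chance of p<0.05 |
|---|---|---|---|
| 30% | 5% | 1.5 | 8% |
| 30% | 10% | 3.0 | 17% |
| 30% | 20% | 6.0 | 53% |
| 30% | 33% | 10.0 | 94% |
| 77% | 5% | 3.9 | 27% |
| 77% | 10% | 7.7 | 74% |

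30% is the planning value, and 77% is the top of the PIM range cited under Sample size.

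**5. The opposite direction.** Suppose the planned effect is real (30% to 20%) but fuller charts add a net 3 points of PIM in 2013 (also an assumption). The observed comparison is 30% against 23%: d = 0.07, se₀ = 0.02942, se₁ = 0.02933, and Φ((0.07 − 1.96·0.02942)/0.02933) = 0.66. Power falls from 93.5% to about 66%.

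**6. What the planned data can show.** Admission PIMs are rated in both years and compared between groups. Number of diagnoses and the Charlson Index are collected in both. A shift in charting could show in any of these. None of them says which criteria moved, and opposite movements can cancel in a count.

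**The case against.** The case against is strong on four points.

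- **The checklist does not ask for documentation.** This stands. A reader might infer that the intervention instructs physicians to write down indications; section 4.1 asks them only to consider the relevant points. Fuller charting is a possible by-product.
- **The direction is not established.** This stands too. A reader might infer a bias in favour of the checklist. That fits criteria that fail for want of an indication, but drug-disease PIMs, omissions and longer reconciled drug lists push the other way.
- **The protocol already holds internal checks.** Largely right. Most admission drugs were presumably chosen before hospital physicians could apply the checklist, so re-labelling alone should also move admission PIM prevalence. Number of diagnoses and Charlson bear on how fully diagnoses are recorded. Unchanged drug counts and class-level prescription prevalence alongside fewer inappropriate ratings would point to charting. So it would be too strong to say that a charting effect cannot be separated at all. What remains is that the protocol gives these comparisons no such role, that reconciliation can itself change the 2013 admission list, and that counts cannot identify the criteria affected.
- **A sensitivity analysis belongs in a statistical analysis plan.** Fair: that plan is not shown, and the absence of the analysis from the protocol is no fault. But the content of the case report form is fixed in the protocol, and an analysis restricted by criterion cannot be run on that form's data unless the criterion is recorded.

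It is also true that the outcome uses STOPP/START and not the Medication Appropriateness Index, so only part of the ratings is open to this. Nor does the protocol confine the raters to notes from the index stay, so a wider record search is no separate demand.

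**Conclusion.** The point holds in a limited form. PIM, PPO and appropriateness ratings rest on records kept by physicians who receive the checklist in one period only, and the form keeps too little to trace a change in charting to particular criteria. Whether charting will change, in which direction and by how much cannot be determined from the documents.

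The figures show only how sensitive the comparison would be. At 30% prevalence, a net re-rating of 10% to 20% of PIM patients would raise the chance of a significant result with no true effect from 5% to about 17% to 53%, and a third would reproduce the whole planned difference. A net shift the other way could hide a real effect. These rest on an assumed f, the planning prevalence of 30% read as a between-group comparison at discharge, and a two-sided test with 450 per group. They are not estimates of the bias in this trial.

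The number of drugs at discharge is unaffected. The plan contains no error of arithmetic or contradiction on this point. It is a cheap improvement to a stated data-collection list, best made before data extraction.

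**What to change.** 1. Add to the case report form (Data collection) the STOPP or START criterion code for every PIM and PPO, at admission and discharge, in both years.
2. Before rating begins, list the criteria that can be rated without a recorded indication. Pre-specify a sensitivity analysis of the discharge PIM comparison limited to them. Judge it against the main result on direction and on relative effect with its confidence interval. Do not require equal absolute differences: the restricted set has a lower prevalence, so a genuine effect will give a smaller one.
3. Report the 2012 against 2013 comparison of admission PIM prevalence and number of diagnoses explicitly as a check on charting drift.

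**Cost.** One extra code per PIM or PPO that the raters identify anyway, and one additional analysis. The restricted set will have lower prevalence and less precision, so it can support or question the main result but not replace it.

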# Objectives

The primary aim of this study among patients aged ≥ 65 years admitted with an acute illness to an internal medicine unit of a community hospital in north western Switzerland is:

1. To assess the efficacy and safety of a simple prescriber checklist for reducing inappropriate prescribing and polypharmacy.

Secondary aims are:

1. To assess the number of prescribed drugs, the prevalence of polypharmacy (concomitant use of ≥ 5 drugs) and hyperpolypharmacy (concomitant use of ≥ 10 drugs).
2. To assess the prevalence of potentially inappropriate medicine use (PIMs; according to STOPP criteria) and of potentially inappropriate prescribing omissions (PPOs; according to START criteria).
3. To assess the prevalence of prescription and the rate of inappropriate prescription of following drugs: non-steroidal anti-inflammatory drugs (NSAID); proton pump inhibitors (PPI); systemic corticosteroids; metamizol-natrium (Novalgin™); potent opiates.

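### Safety is part of the primary aim, but its only measure is 30-day readmission, with no death recorded and no sizing or tolerable increase set for it

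*Protocol*

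**What the plan says.** The single primary aim under Objectives is "To assess the efficacy and safety of a simple prescriber checklist for reducing inappropriate prescribing and polypharmacy". Safety is then given one measure, under Follow-up: "As safety parameter we will assess the all-cause re-hospitalisation rate at 30 days after discharge using administrative data of the hospital". Only returns to the study hospital count, which the protocol defends on the ground that it is the only hospital in its area.

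Under Outcomes, the primary outcome concerns prescribing only. It begins "The primary outcome is the reduction of the proportion of patients using inappropriate drugs (PIM) at discharge" and adds the number of drugs at discharge. The safety measure, "the all-cause rehospitalisation rate at 30 days after discharge", is the third secondary outcome.

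The case report form items under Data collection end with "all-cause re-hospitalisation at 30 days". Death, in hospital or after discharge, is not among them.

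Under Sample size, the calculation takes a prevalence of inappropriate prescribing and/or polypharmacy falling "from 30% at admission to 20% at discharge", "with a probability (power) of 90% at a significance level of 0.05". No readmission rate or tolerable increase in readmission appears anywhere. Under Statistical methods, categorical variables "will be compared using the chi-squared test or Fisher’s exact test for categorical variables" and continuous ones by the Mann-Whitney U test. The variables listed in that sentence do not include re-hospitalisation.

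**The concern.** A checklist meant to reduce prescribing raises a question of harm, and the protocol puts that question in its primary aim. The evidence planned for it has two weaknesses.

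First, readmission can only be observed in someone who leaves hospital alive and survives long enough to return. If the two cohorts differ in mortality, the readmission rate can stay level or even fall as outcomes get worse. An analysis plan could not repair this later, because it cannot analyse a variable that was never recorded.

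Second, showing safety means excluding an increase of a stated size. The protocol states no such size, does not size the study for readmission, and names only tests of difference. A non-significant comparison could then arise either from a true absence of harm or from too little information.

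**Working it through.** **Inputs from the protocol.** 450 patients per group; significance level 0.05; power 90%; prevalences 30% and 20%; stated requirement 412 per group (Sample size and Table 1).

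**Assumed, because the protocol gives no figure.** Readmission rates of 5, 10, 15 and 20%; increases of 3 and 5 percentage points; the mortality figures in step 2.

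**Step 1: the protocol's own sample size.** For two proportions, two-sided:

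n = [1.96·√(2·0.25·0.75) + 1.2816·√(0.30·0.70 + 0.20·0.80)]² / 0.10² = (1.2003 + 0.7795)² / 0.01 = 392.

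With the continuity correction, (n/4)·[1 + √(1 + 4/(n·0.10))]² = 412. This matches the stated figure, and the other six rows of Table 1 also reproduce in this way. The calculation is sound for prescribing, but readmission does not enter it.

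**Step 2: what the missing death item can do.** Suppose survivors are readmitted at 12% in both years, 30-day mortality after discharge is 4% in 2012 and 8% in 2013, and those who die are not readmitted first.

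- Readmission: 0.12 × 0.96 = 11.5% against 0.12 × 0.92 = 11.0%, a fall of 0.5 points.
- Death or readmission: 4 + 11.5 = 15.5% against 8 + 11.0 = 19.0%, a rise of 3.5 points.

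The planned measure would move slightly in the reassuring direction while the composite worsened.

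**Step 3: what 450 per group can say about readmission.** Let r be the common true rate, d the increase and SE = √(2r(1−r)/450).

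- Half-width of the 95% confidence interval for the difference: 1.96·SE.
- Probability that the upper limit lies below d when the true rates are equal: Φ(d/SE − 1.96).
- Power of a two-sided difference test for a true rise d: Φ[(d − 1.96·SE₀)/SE₁], where SE₀ uses the pooled rate and SE₁ the two separate rates.

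Example at r = 10%: SE = √(0.18/450) = 0.020. For d = 0.03, Φ(1.50 − 1.96) = 32%. For d = 0.05, Φ(2.50 − 1.96) = 71%.

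| Assumed rate | Half-width (points) | Exclude 3 points | Exclude 5 points | Detect +3 | Detect +5 |
|---|---|---|---|---|---|
| 5% | 2.9 | 54% | 93% | 45% | 81% |
| 10% | 3.9 | 32% | 71% | 29% | 62% |
| 15% | 4.7 | 24% | 56% | 23% | 51% |
| 20% | 5.2 | 20% | 47% | 19% | 44% |

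For 80% probability of excluding 3 points, the required number per group is 829, 1570, 2224 and 2791 at the four rates. For 5 points it is 299, 566, 801 and 1005.

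The table takes all 450 as discharged alive, so in-hospital deaths would lower these figures a little. A death-or-readmission composite has a higher rate and a wider interval: at an assumed 25%, the half-width is 1.96·√(2·0.25·0.75/450) = 5.7 points.

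**The case against.** Much of what a reader might infer here is not in the text.

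- **Testing and handling of deaths.** A reader might conclude that readmission will be tested by chi-squared, that deaths will be scored as non-events, and that a non-significant result will be read as safe. The protocol states none of these. The sentence naming the tests does not list re-hospitalisation, no rule for deaths is given, and Follow-up says only that the rate will be assessed. The choice of test, an interval rule and the handling of deaths could also properly sit in an analysis plan that is not at hand. This part of the objection stands, and these omissions are not the finding. It does not reach the missing death item or the mismatch between the primary aim and an unsized secondary outcome.

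- **Size of increase.** A reader might also infer that the study cannot exclude any relevant increase, or would usually miss one. That goes too far. No tolerable increase is defined. At a 5% rate a 5-point increase is excluded with 93% probability, and a difference test detects a 5-point rise with 62% and 51% power at 10% and 15%. The limitation is clear for 3 points and depends on the base rate for 5.

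- **Size of the death effect.** The distortion of readmission itself is small. In the example, doubling mortality shifts it by 0.5 points against a half-width of 4.2 points at 12%. A patient readmitted before dying is still counted, and a rate measured after discharge already implies patients discharged alive. All of this is fair. The weakness is that readmission would not show the excess deaths, whatever its own bias.

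**Conclusion.** The point holds within these limits. Safety belongs to the primary aim, yet the data listed support only a readmission rate at one hospital, with no record of deaths in hospital or of deaths after discharge without readmission. Following the protocol exactly would give a safety result that is blind to those deaths.

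A non-significant readmission comparison would not by itself support safety. Over assumed rates of 5 to 20%, the study has a 20 to 54% probability of excluding a 3-point increase when none exists, and 47 to 93% for a 5-point increase. These ranges rest on assumed rates and margins, and the mortality example is illustrative. Nothing here undermines the prescribing outcomes or their sample size. The change is worth making because it costs little and alters what may be concluded about safety.

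**What to change.** 1. Under Data collection, add in-hospital death and vital status at 30 days after discharge to the case report form for both cohorts, as far as the hospital's records show them.
2. Tabulate in-hospital deaths by cohort.
3. Among patients discharged alive, report readmission, and death or readmission, each as a risk difference (2013 minus 2012) with a 95% confidence interval.
4. Base any safety statement on the upper confidence limit, not on a p-value above 0.05.
5. State under Objectives or Sample size that the study is not sized to exclude small increases in readmission. The interval half-width should not be offered as the increase the study can exclude: with equal true rates, an increase of exactly that size is excluded only about half the time, since Φ(1.96 − 1.96) = 50%.

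The cost is two extra items per patient and some analysis wording, with no additional patients. The protocol names administrative data only for re-hospitalisation, so the availability of death status needs confirming. Out-of-hospital deaths may be incompletely captured in both years and should be reported as a limitation. The safety claim becomes weaker.
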